## Abstract

**Background:**

Neurological disorders, including Parkinson’s disease (PD), are among the leading causes of disability worldwide. One of the major challenges of this disease is chronic fatigue, which is considered one of the most common and debilitating non-motor symptoms. Increased fatigue in these patients reduces their self-efficacy, which directly correlates with decreased quality of life (QOL) and worsening motor and non-motor symptoms. Given the profound impact of PD on patients’ daily lives, adopting effective approaches to improve their QOL is essential.

The continuous care model (CCM), designed as an indigenous approach based on Iran’s cultural and social characteristics, can serve as an effective strategy for managing complications associated with PD.

**Methods:**

This study is a clinical trial aimed at evaluating the effect of the CCM on fatigue, self-efficacy, and QOL in patients with PD in Isfahan, Iran. A total of 80 patients will be selected through convenience sampling and randomly assigned to either the intervention or control group. Data will be collected using standardized questionnaires at three time points: before the intervention, immediately after, and 1 month later. In the intervention group, the CCM will be implemented over a nine-week period in four stages: familiarization, sensitization, control, and evaluation. The control group will receive only routine pharmacological care. Data will be analyzed using descriptive statistics (mean and standard deviation), followed by repeated measures ANCOVA to compare changes in outcomes across three time points between groups, controlling for covariates. Normality and homogeneity of variances will be assessed using the Kolmogorov–Smirnov and Levene’s tests, respectively.

**Discussion:**

Various approaches have been proposed to manage fatigue, enhance self-efficacy, and improve QOL in patients with PD; however, many of these strategies face challenges, including the lack of a comprehensive approach. The CCM focuses on the care of patients with chronic conditions, emphasizing education and empowerment for both patients and their families. By placing the patient at the center of care, this holistic approach plays a crucial role in the management of chronic diseases.

**Trial registration.:**

It is registered in the Iranian Registry of Clinical Trials (IRCT) with the registration number IRCT20190712044181N7.

**Supplementary Information:**

The online version contains supplementary material available at 10.1186/s13063-025-09057-5.

## Administrative information

Note: the numbers in curly brackets in this protocol refer to SPIRIT checklist item numbers. The order of the items has been modified to group similar items (see http://www.equator-network.org/reporting-guidelines/spirit-2013-statement-defining-standard-protocol-items-for-clinical-trials/).

## Introduction

### Background and rationale {6a}

PD is the second most common neurodegenerative disorder, with its burden increasing as the global population ages [1, 2]. Over the past 25 years, the prevalence of PD has doubled worldwide, with more than 8.5 million cases recorded in 2019. Additionally, PD has resulted in 5.8 million disability-adjusted life years (DALYs) and 329,000 deaths, showing a significant increase compared to the year 2000 [3]. In Iran, a 2021 study reported that the prevalence of PD among individuals over 50 years old was 261.1 per 100,000, with the highest rate observed in Isfahan [4]. It is estimated that by 2050, the global burden of PD will exceed 12 million cases [5].

PD affects physical, psychological, and cognitive functions, significantly impacting patients, their families, and society [6]. Bradykinesia, muscle rigidity, and postural instability make daily activities challenging, while anxiety, depression, and cognitive issues further reduce QOL and personal independence [7].

In recent decades, the non-motor symptoms of PD, particularly fatigue, have gained significant importance in its diagnosis and management [8]. Fatigue is one of the most common and disabling symptoms of PD, often appearing in the early stages and persisting throughout the disease [9]. Affecting more than half of patients, fatigue leads to weakness, physical deterioration, and reduced ability to work, engage in social activities, and exercise [10, 11]. The prevalence of fatigue among PD patients ranges between 33 and 58% [10] and has been reported to negatively impact their professional and social lives [12]. Many patients consider fatigue to be their most distressing symptom, yet effective treatments remain limited [11]. Therefore, recognizing and managing fatigue is crucial for improving patients’ QOL [10].

Studies indicate that fatigue and other non-motor symptoms of PD are strongly associated with reduced self-efficacy [13]. Self-efficacy, defined as an individual’s perceived ability to perform tasks [13], is generally low in PD patients [14] and plays a key role in disease management and QOL [13]. Among non-motor symptoms, depression and apathy have a greater impact on self-efficacy than motor symptoms and can contribute to its decline even in the early stages of the disease. Patients with lower self-efficacy typically experience a poorer QOL [13].

Poor fatigue management and reduced self-efficacy in PD patients contribute to a decline in QOL [15]. According to the World Health Organization (WHO), QOL encompasses physical health, psychological well-being, social relationships, and environmental factors [16]. Compared to healthy individuals, PD patients experience lower QOL, particularly in terms of physical functioning and mental health [17]. As the disease progresses, it leads to disability, physical and psychological complications, and a further decline in QOL [18].

Several factors significantly impact health-related quality of life (HRQOL) in PD, including depression, disease severity, motor impairments, cognitive dysfunction, and non-motor symptoms such as fatigue and pain. These symptoms worsen as the disease advances, further compromising patients’ well-being [19, 20]. Therefore, implementing effective interventions to enhance the QOL of PD patients is crucial [17].

Current treatments for PD primarily focus on motor symptoms, but a more comprehensive approach is necessary [13]. Integrating nursing care with pharmacological treatment has been shown to reduce depression, improve sleep quality, and enhance patients’ QOL [18]. Continuity of care is a fundamental concept in nursing, referring to the provision of ongoing care to address patients’ health needs [21]. The indigenous model of continuous care, developed by Ahmadi et al., has been effective in improving outcomes such as hospitalization rates, physician visits, lipid levels, and QOL in cardiac patients [22, 23]. This model strengthens the connection between patients and healthcare providers, thereby promoting adherence to healthy behaviors [24].

The CCM consists of four interrelated stages: familiarization (establishing mutual understanding and motivation among patients and their families), sensitization (engaging patients and families with the disease and its complications), control (internalizing healthy behaviors), and evaluation (assessing the model’s effectiveness). This model helps increase patients’ willingness to adopt healthier behaviors [23].

The CCM has been extensively studied in different patient populations, demonstrating positive effects on QOL in heart failure patients [25], self-efficacy in myocardial infarction patients [26], QOL in hemodialysis patients [27], treatment adherence in hemodialysis patients [28], caregiver burden in stroke patients [29], insomnia in pregnant women [30], and sleep quality in older adults [31]. Additionally, a study on multiple sclerosis patients showed that this model significantly improved their QOL [32]. Overall, most studies have reported positive effects of this model on various health outcomes [23].

However, some studies have reported no significant effects of the CCM on certain health outcomes. For instance, one study found that this model did not improve dialysis adequacy in hemodialysis patients [33]. Additionally, research on the QOL of schizophrenic patients indicated that while the model was effective in enhancing interpersonal relationships, it had no significant impact on other dimensions of QOL [34]. Moreover, a study on children with nephrotic syndrome revealed that the model did not reduce the recurrence of the disease [35].

As highlighted earlier, numerous studies have confirmed the positive impact of the CCM on various aspects of disease management, patient outcomes, and caregiver burden. However, some research has reported limited or no effects in specific contexts. Given the high prevalence of PD in Iran and globally, along with the anticipated increase in the aging population, evaluating the effectiveness of this model in reducing disease-related challenges and improving patients’ self-management is crucial. Notably, the CCM, as an indigenous approach tailored to Iran’s cultural and social characteristics, may offer distinct advantages over other methods.

Thus, this study was designed to evaluate the impact of a CCM-based intervention on fatigue, self-efficacy, and QOL in patients with PD.

### Objectives {7}

This study is a randomized controlled clinical trial designed to examine the effectiveness of a CCM-based program on fatigue, self-efficacy, and QOL in patients with PD attending the Parkinson’s Association of Isfahan Province. The effectiveness of this intervention will be assessed using the Parkinson’s Disease Fatigue Scale 16** (**PFS-16), General Self-Efficacy Scale (GSE-17), and Parkinson’s Disease Questionnaire-8 (PDQ-8).

This study aims to improve the condition of patients by implementing a structured intervention based on the CCM. The findings may play a significant role in optimizing care services for individuals with PD.

### Trial design {8}

This study is a randomized controlled clinical trial that includes random allocation of participants, a control group, and an interventional approach to assess the effect of a CCM-based program on fatigue, self-efficacy, and QOL in patients with PD. The study follows a parallel two-group, multivariable design with assessments conducted before the intervention, immediately after, and 1 month post-intervention.

This trial is designed as a superiority trial to evaluate whether the CCM-based program is more effective than standard care in improving fatigue, self-efficacy, and quality of life in patients with Parkinson’s disease.

## Methods: participants, interventions, and outcomes

### Study setting {9}

The Isfahan Parkinson’s Charity Association was selected as the study site due to its accessibility to patients and the presence of documented medical records confirming PD diagnosis.

Established under registration number 6902, this nonprofit organization was founded through the efforts of philanthropists and neurology specialists to support individuals with PD. The association aims to provide education, raise awareness, facilitate prevention, support treatment and rehabilitation, and offer humanitarian assistance to patients and their families.

### Eligibility criteria {10}

#### Inclusion criteria

Patients eligible for participation in the study must meet the following criteria:Confirmed diagnosis: diagnosis of PD confirmed by a qualified neurologist specialized in movement disorders, based on the UK PD Society Brain Bank criteria [17].Willingness to participate: patients must express willingness to take part in the study [13, 36].Cognitive function: absence of cognitive impairment, confirmed by a neurologist’s evaluation [9, 37].Physical health: no severe physical illnesses that would prevent participation [38].Mental health: no acute or chronic psychiatric disorders [37].Neurological health: no history of acute or chronic neurological disorders, such as stroke or traumatic brain injury [37].Sensory abilities: no hearing or vision impairments that hinder participation [36].Literacy: ability to read and write [39].Medication use: no current use of psychiatric medications [39].Language: native Persian speakers.Family involvement: at least one family member must attend educational sessions alongside the patient.No concurrent interventions: patients must not participate in any other educational sessions or treatment-care interventions related to PD during the study period.

#### Exclusion criteria

Patients will be excluded from the study if they meet any of the following conditions:Hospitalization: need for hospital admission during the study period.Absenteeism: absence from more than two sessions [39].Lack of cooperation: failure to actively participate or express unwillingness to continue [39].Cognitive decline: development of cognitive impairments during the study [9].

### Who will take informed consent? {26a}

Before participation, all eligible patients will receive both oral and written information about the study, including its objectives, procedures, potential risks and benefits, and their rights as participants. Adequate time will be given for questions and consideration.

Informed written consent will be obtained by the researcher, [name] [name], a master's student in nursing and the person responsible for conducting the intervention.

### Additional consent provisions for collection and use of participant data and biological specimens {26b}

Not applicable. No biological specimens will be collected, and no additional consent is required for ancillary studies.

## Interventions

### Explanation for the choice of comparators {6b}

The control group will receive routine care, which represents the standard nursing and medical practices currently implemented in the study setting. This comparator was chosen to evaluate the effectiveness of the intervention against the usual level of care and to ensure the results are applicable to real-world clinical conditions.

### Intervention description {11a}

After obtaining approval from the School of Nursing and Midwifery, Isfahan University of Medical Sciences, and presenting it to the officials of the Parkinson’s Charity Association, the researcher will enter the study setting and select participants based on inclusion criteria and neurologist confirmation. After obtaining written informed consent, participants will complete baseline questionnaires (demographic and clinical information form, PFS-16, GSE-17, and PDQ-8) in a 30–45-min session.

Participants will then be randomly assigned to either the intervention group (*n* = 40) or the control group (*n* = 40) using block randomization. After completing consent forms and baseline assessments, the CCM—comprising four stages: familiarization, sensitization, control, and evaluation—will be implemented for the intervention group over a period of 8 weeks (2 months).

The control group will receive no intervention and will continue with standard medical treatment and routine care as prescribed by their physician [40].

In the first phase of the CCM, known as the familiarization stage, the study participants in the intervention group (including the patient and their caregiver) attend a session lasting approximately 30 to 45 min. This session takes place in a quiet room with appropriate lighting and temperature, free from environmental distractions, within the Parkinson’s Association.

During this stage, the nurse is introduced to the patient and their caregiver, and the expectations of the nurse at different stages of the study are outlined. Additionally, the expectations and needs of the patient and caregiver are identified. Recommendations are provided regarding the importance of continuity in the caregiving relationship and minimizing interruptions until the designated period ends. Moreover, the schedule for in-person and telephone follow-ups is established, and the objectives and means of communication, along with the structure of educational sessions, are explained [40].

The second phase of the CCM, known as the sensitization stage, aims to enhance the awareness of patients and their families regarding the nature of the disease, its early and late complications, preventive measures, and associated limitations. This stage actively involves both the patient and their family in addressing the chronic condition and encourages the adoption of appropriate health behaviors.

During the sensitization stage, participants in the intervention group will attend weekly sessions for four consecutive weeks (a total of four sessions), with each session lasting approximately 30 to 45 min. These sessions will take place in a quiet room with appropriate lighting and temperature, free from environmental distractions, within the Parkinson’s Association. To improve the effectiveness of the training, educational slides and pre-recorded videos on PD will be used.

The key activities in this phase primarily involve care counseling, which will be conducted in group sessions. The main topics covered in these follow-up care sessions (as outlined in Table 1) include an explanation of PD and its symptoms in a way that is comprehensible to patients and their families, the acute and chronic complications of the disease and their management, the importance and implementation of a proper diet and physical activity, and the significance of adhering to prescribed medications. Together, the first and second phases constitute the initial month of the intervention program [40].

**Table 1 Tab1:** Content of the sessions conducted for the intervention group

Stage	Educational behavioral objectives	Content	Teaching method	Presenter	Duration
First stage: the familiarization stage	• Learners should express their expectations regarding CCM sessions • Scheduling in-person meetings in consultation with patients and their companions • Gathering feedback from learners on the objectives of CCM sessions	• Introducing the nurse to the patient and their companion, clarifying the nurse’s expectations at different stages of the study • Identifying and addressing the expectations and concerns of the patient and their companion • Providing recommendations on the necessity of continuity in the care relationship, emphasizing minimal disruption until the designated period ends • Establishing and agreeing on schedules for in-person and phone meetings, outlining the objectives and methods of communication and educational sessions	• Lecture • Q&A (Question and Answer) • Group Discussion	Researcher	30 to 45 min
Second stage: sensitization phase	• Learners should be able to describe the nature and symptoms of the disease • They should identify the primary and secondary symptoms of PD and distinguish them from other conditions • They should interpret information related to PD and explain the significance of each symptom in disease progression	• Explaining PD and its symptoms in a way that is understandable for patients and their families • Describing how the disease affects daily activities, social interactions, and the emotional well-being of patients	• Lecture • Group Discussion • Q&A • Posing questions aligned with educational objectives and allowing patients to respond	Researcher	30 to 45 min The first 10 min of the session will be allocated to an icebreaker activity
Third stage: sensitization phase	• Learners should be able to identify complications of a specific disease in a real-life scenario and propose the best management strategies • They should analyze the impact of not using prescribed medications on disease progression • Learners should be capable of designing a care plan to manage acute and chronic complications that may arise in themselves	• Acute and Chronic Complications of the Disease and Their Management • The Importance of Adhering to Prescribed Medications	• Lecture • Group Discussion • Q&A • Presentation of a Scenario by the Researcher to Patients and Receiving Their Responses	Researcher	30 to 45 min
Fourth stage: sensitization phase	• Learners should be able to propose appropriate solutions for managing symptoms and signs in three real-life scenarios	Management of PD Symptoms and Signs	• Lecture • Group Discussion • Q&A • Presentation of a Scenario by the Researcher to Patients and Receiving Their Responses	Researcher	30 to 45 min
Fifth stage: sensitization phase	• Learners should be able to design a healthy meal plan for 1 day • Learners should explain the benefits of physical activity in PD to their peers • Learners should list several simple strategies to enhance home safety • Learners should select appropriate assistive devices to facilitate walking • Learners should develop a simple plan to reduce the risk of slipping in the bathroom	• The Importance of Diet and How to Follow It • The Importance of Physical Activity and How to Maintain It • Strategies for Increasing Home Safety and Using Assistive Devices to Facilitate Walking and Maintain Balance	• Lecture • Group Discussion • Q&A	Researcher	30 to 45 min
Sixth stage: control phase	• Learners are expected to have sufficient knowledge of previous sessions and actively share their understanding during the review of past topics • Learners should express any questions or challenges they face and implement the solutions provided by the researcher • Learners should actively describe the health behaviors they have adopted since completing the sensitization sessions	• Continuation of Continuous Care Consultations to Sustain Health Behaviors Based on Patients’ Needs and Challenges • Encouraging Patients to Maintain Healthy Behaviors	• Phone Call and Q&A	Researcher	30 to 45 min
Seventh stage: control phase	• Learners are expected to have sufficient knowledge of previous sessions and actively share their understanding during the review of past topics • Learners should express any questions or challenges they face and implement the solutions provided by the researcher • Learners should actively describe the health behaviors they have adopted since completing the sensitization sessions	• Continuation of continuous care Consultations to Sustain Health Behaviors Based on Patients’ Needs and Challenges • Encouraging Patients to Maintain Healthy Behaviors	• Phone Call and Q&A	Researcher	30 to 45 min
Eighth stage: control phase	• Learners are expected to have sufficient knowledge of previous sessions and actively express their understanding during the review of past topics • Learners should articulate any questions or challenges they face and implement the solutions provided by the researcher • Learners should actively describe the health behaviors they have adopted since the completion of the sensitization sessions	• Continuation of continuous Care Consultations to Sustain Health Behaviors Based on Patients’ Needs and Challenges • Encouraging Patients to Maintain Healthy Behaviors	• Phone Call and Q&A	Researcher	30 to 45 min
Ninth stage: control phase	• Learners are expected to have sufficient knowledge of previous sessions and actively express their understanding during the review of past topics • Learners should articulate any questions or challenges they face and implement the solutions provided by the researcher • Learners should actively describe the health behaviors they have adopted since the completion of the sensitization sessions	• Continuation of continuous Care Consultations to Sustain Health Behaviors Based on Patients’ Needs and Challenges • Encouraging Patients to Maintain Healthy Behaviors	• Phone Call and Q&A	Researcher	30 to 45 min
Tenth stage: evaluation phase	• Completion of Questionnaires by Participants • Learners should express any new or unresolved issues and listen to the solutions provided by the researcher or the experiences of other participants regarding the existing problem	• Review of the Care Process, Evaluation of Key Indicators through Recompletion of Questionnaires, and Monitoring and Controlling Patient Behavior and the Impact of Provided Training • Assessment of Unresolved Issues or the Emergence of New Problems	• Lecture • Q&A • Group Discussion	Researcher	30 to 45 min

In the monitoring phase, follow-up care counseling continues to reinforce the maintenance of healthy behaviors. This phase is carried out over 4 weeks through four telephone calls (one call per week) with the patient and, if necessary, with their caregiver. The content of these calls is tailored to the patient's specific problems and needs.

A key component of this phase is encouraging the patient to sustain healthy behaviors and referring them to a specialist if required. Additionally, a contact number will be provided to patients and their caregivers, allowing them to reach out with any questions and receive necessary guidance [40].

The evaluation phase, which is the final step of the intervention, involves assessing the care process, evaluating key indicators through the reassessment of questionnaires, and monitoring the patient’s behavior to determine the impact of the provided education. Additionally, any unresolved issues or newly emerging problems will be examined [40].

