### Outcomes {12}

The primary outcome is quality of life, measured using the PDQ-8, at 1 month post-intervention to assess sustained effects. Secondary outcomes include fatigue (PFS-16) and self-efficacy (GSE-17), assessed at baseline, immediately post-intervention, and 1 month post-intervention. Data collection will be coordinated via telephone, and participants will be asked to visit the Isfahan Parkinson’s Charity Association to complete the questionnaires. If a participant is unable to attend, the researcher will complete the questionnaire at the participant’s residence.

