### Participant timeline {13}

#### Sample size {14}

To determine the sample size, assuming a normal distribution of quality-of-life data, the following formula will be used.$$n= \frac{2 \times {\sigma }^{2}{ \times ({Z}_{1-\beta }+ {Z}_{1-\alpha /2})}^{2}}{{({\mu }_{1}-{\mu }_{2} )}^{2}}$$

The standard deviation in the study by Moghtaderi et al. was reported to be approximately 6 [41]. Therefore, with a power of 80% (1 − β = 80%) and assuming a confidence level of *α* = 0.05, the required sample size for each group to detect a difference of 4 units (μ₁ − μ₂ = 4) is:$$n=\frac{2 \times {6}^{2} \times {(0.84+ 1.96)}^{2}}{{(4)}^{2}}=35.28\approx 36$$

The required sample size for each group will be 36 participants, resulting in a total of 72 samples. Considering a 10% dropout rate, a total of 80 participants will be required for the study.

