## Statistical methods

### Statistical methods for primary and secondary outcomes {20a}

For data analysis, descriptive statistics, including mean and standard deviation, will first be calculated. In inferential statistics, to compare changes in the three quantitative variables across three time points (before the intervention, immediately after the intervention, and 1 month later) between the control and intervention groups, repeated measures analysis of covariance (ANCOVA) will be used, controlling for covariates. The Kolmogorov–Smirnov test will be applied to assess data normality, while Levene’s test will be used to examine variance homogeneity. All analyses will be performed using SPSS software, version 25.

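### The intervention is given in groups in one arm only, and neither the sample size nor the ANCOVA allows for correlation within session group, so the stated 80% power and 5% error are not assured

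*Protocol article*

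**What the plan says.** Patients are randomised individually, 40 to each arm (Sequence generation {16a}). Under Intervention description {11a}, the key activities of the four weekly sensitization sessions "primarily involve care counseling, which will be conducted in group sessions". Table 1 lists group discussion as a teaching method for every stage not held by telephone. In the evaluation stage, participants are to "listen to the solutions provided by the researcher or the experiences of other participants regarding the existing problem". The four control-phase contacts are individual telephone calls, and the researcher presents every session. The comparison arm continues with routine care and has no sessions.

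Sample size {14} uses the formula for two independent means, with a standard deviation that "was reported to be approximately 6", a difference of 4 units, 80% power and two-sided α = 0.05. It concludes: "The required sample size for each group will be 36 participants, resulting in a total of 72 samples". With 10% dropout this becomes 80. No group size, ICC or design effect appears.

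For the analysis, {20a} says that "repeated measures analysis of covariance (ANCOVA) will be used, controlling for covariates". The covariates are not named, and a session-group term is not mentioned. Under Outcomes {12}: "The primary outcome is quality of life, measured using the PDQ-8, at 1 month post-intervention".

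**The concern.** Group discussion, an icebreaker and the exchange of experience are meant to let participants influence one another. Patients who sit in the same group may therefore finish with more similar PDQ-8 scores than patients in different groups. Controls have no such grouping, so this is a partially nested design: clustered in one arm, independent in the other.

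If within-group correlation is present and ignored, the variance of the intervention mean is understated. The interval for the primary comparison is then too narrow, its p-value too small, and the power lower than {14} states. Fatigue and self-efficacy are analysed by the same method, so they share the problem.

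**Working it through.** **Inputs from the protocol.** SD 6, difference 4, two-sided α 0.05 (z = 1.96), power 80% (z = 0.84), 36 evaluable per arm, 10% dropout.

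**Inputs assumed, because the protocol does not give them.** Group size m = 5 to 10; ICC = 0.01 to 0.10; fixed group membership; total SD held at 6.

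**1. The plan's own figure.** n = 2 × 36 × (0.84 + 1.96)² / 16 = 35.28, rounded up to 36 per arm, 72 in total; 72 / 0.9 = 80. This reproduces. With 36 independent patients per arm, power is 80.7% by the normal approximation and 79.7% by the t distribution.

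**2. Clustering in the intervention arm only.**
- Design effect for that arm: DE = 1 + (m − 1) × ICC.
- Variance of the difference: V = (36/36) × DE + 36/36 = 1 + DE. Under independence V = 2.
- Power of a test with the correct standard error: Φ(4/√V − 1.96).
- Type I error of the test that ignores groups: 2 × [1 − Φ(1.96 × √(2/V))].

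| m | ICC | DE | V | Power | Naive type I error |
|---|---|---|---|---|---|
| 5 | 0.01 | 1.04 | 2.04 | 80.0% | 5.2% |
| 10 | 0.01 | 1.09 | 2.09 | 79.0% | 5.5% |
| 5 | 0.05 | 1.20 | 2.20 | 76.9% | 6.2% |
| 10 | 0.05 | 1.45 | 2.45 | 72.4% | 7.7% |
| 5 | 0.10 | 1.40 | 2.40 | 73.3% | 7.4% |
| 10 | 0.10 | 1.90 | 2.90 | 65.1% | 10.4% |

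Example, m = 10 and ICC 0.05: 4/√2.45 − 1.96 = 0.60, so power is 72.4%; 1.96 × √(2/2.45) = 1.77, so the error is 7.7%. Simulated two-sample t-tests with 36 per arm and groups of 9 gave errors of 5.5%, 7.2% and 9.8% at ICC 0.01, 0.05 and 0.10, in line with the formula.

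**3. What baseline adjustment does.** Assume a correlation of 0.5 between baseline and 1-month PDQ-8, and group variance that arises after baseline and so is not reduced. Residual variance per patient is 36 × (1 − 0.25) = 27. For m = 10, DE = 1 + 9 × (36 × ICC)/27 and V = (27/36) × (1 + DE). The naive error is 2 × [1 − Φ(1.96 × √(2/(1 + DE)))].

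| ICC | DE | V | Power | Naive type I error |
|---|---|---|---|---|
| 0.01 | 1.12 | 1.59 | 88.7% | 5.7% |
| 0.05 | 1.60 | 1.95 | 81.7% | 8.6% |
| 0.10 | 2.20 | 2.40 | 73.3% | 12.1% |

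Power improves in every row. The error rate becomes slightly worse, because the group variance is now a larger share of a smaller residual.

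**4. Whether the remedy works.** In a simulation with four groups of 10, a partially nested test with Satterthwaite degrees of freedom had a type I error of about 5.2-5.6% over ICC 0 to 0.10. The interval was wider than the naive one by about 6-9% at ICC 0.01-0.02, 18% at 0.05 and 31% at 0.10. With so few groups these figures depend on how the group variance is estimated and should be read as rough.

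**The case against.** Several features point to a low ICC. One researcher presents every session, so differences between presenters cannot create group differences. Slides and pre-recorded videos standardise the content. The group sensitization amounts to four sessions of 30 to 45 minutes, followed by four individual calls. The primary outcome is measured 1 month after the programme ends. Missed sessions are rescheduled, and nothing says that group membership is fixed, so clean nesting is itself an assumption. At ICC 0.01 the harm is negligible. These points stand. They make a small effect plausible but do not rule out a larger one, and group contact returns in the evaluation session.

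A second objection is that a random effect, its degrees of freedom and a data field commonly belong in an analysis plan, which is not shown here. That is fair for the model details. It does not cover the sample size, which this article fixes with a full formula and no allowance. Nor can a later plan use a group identifier that was never recorded.

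Third, the planned ANCOVA, if it adjusts for baseline, would have more power than the unadjusted formula credits. This is right for power, but section 3 of the working shows that it does not repair the error rate.

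A reader might infer that 80% power and 5% error definitely fail. The documents do not support this: with groups of 5 and ICC 0.01 they are essentially met, and if group membership has no effect on outcomes the 5% level stands. Nor do they support a design effect on both arms, since controls are not grouped.

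**Conclusion.** The point holds as a missing allowance, not as a demonstrated failure. Delivery is in groups in one arm, and both {14} and {20a} as described treat all patients as independent. The stated power and error are therefore conditional on an ICC near zero, which the protocol does not state or justify.

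Under the assumed groups of 5 to 10, the consequence runs from negligible at ICC 0.01 to material at ICC 0.05 and above, where naive error is 6.2-10.4% and unadjusted power 65-77%. The results rest on the assumed group size, ICC and fixed membership, and on a normal approximation that is optimistic with few groups.

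Whether 80 patients are enough cannot be settled from the document. Without baseline adjustment, groups of 10 would need 17.64 × (1 + DE) per arm, where 17.64 = 36 × 2.80²/16. That is 44 per arm (98 enrolled) at ICC 0.05 and 52 per arm (116 enrolled) at ICC 0.10. With an assumed baseline correlation of 0.5, 36 per arm gives about 82% power at ICC 0.05 but only 73% at 0.10. A reader could take either table to mean that the trial must be enlarged, or that it need not be; neither follows without the missing inputs.

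The change is worth making before analysis, because it protects the primary comparison.

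**What to change.** 1. **Record the session group** of each intervention patient, and note any session attended with a different group after rescheduling.
2. **Replace the ANCOVA for the primary outcome** with a baseline-adjusted, partially nested mixed model: 1-month PDQ-8 on arm and baseline PDQ-8, a random session-group effect in the intervention arm only (each control treated as a singleton), and small-sample degrees of freedom such as Satterthwaite. Use the same structure for fatigue and self-efficacy.
3. **Restate the power in {14}** as conditional on the planned group size and an ICC range that includes 0.01, for example 0.01 to 0.10, with the assumed baseline correlation shown.

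The cost is one data field, a changed model and a rewritten power statement. The real downside is statistical. Groups of about 10 mean only about four groups, so the group variance will be poorly estimated, and the interval widens by roughly 5-30% depending on the ICC. The restated power should reflect this. No treatment or visit changes.
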